## 4. STUDY POPULATION

### 4.1 Population (base)

The study population will consist of 40 healthy, non-smoking, normal weight subjects (20 subjects within each condition) matched in BMI, age and gender. Recruitment will take place by advertising around the campus and in local newspapers.

Interested candidates will be sent the information brochure of the study, including the main inclusion criteria. In case the potential subject wants to participate and meets the main inclusion criteria, an appointment will be set for a screening visit.

During the screening:

- An informed consent form needs to be signed by the subject.
- Determination of weight and height, calculation of the Body Mass Index (BMI).
- Determination of waist and hip circumferences.
- One blood sample of 10 mL per subject will be drawn to determine plasma creatinine concentrations in order to estimate the GFR
- Questionnaires will be completed to assess
  - Medical situation at the present time and in the past. An example of this questionnaire is attached to the protocol.
  - Sleeping behaviour. An example of this questionnaire is attached to the protocol.
  - Eating pattern by the Dutch translation of Three Factors Eating Questionnaire (28). This questionnaire consists of three subscales: cognitive restraint of eating, disinhibition of dietary restraint and emotional eating, and perceived hunger. An example of this questionnaire is attached to the protocol.
  - Habitual physical activity by a Dutch translation of the Baecke questionnaire (29). This questionnaire consists of three subscales: work activity, sports activity and non-sports leisure activity. This questionnaire is included in the questionnaire about the medical situation of the subjects attached to the protocol.

The results of the completed questionnaires will be checked on the inclusion and exclusion criteria before assigning the subject to the study population.

## 4.2 Inclusion criteria

- Age between 18 and 35 years
- BMI between 18 and 27 kg/m^2
- Non-smoking
- No sleeping problems
- Normal general health (screening questionnaire)
- No medication that could interfere with the experiment
- Unrestrained eaters (F1 < 9)
- Weight stable (weight change < 3 kg during the last 6 months)
- eGFR  $\geq$  90ml/min/1.73m^2

## 4.3 Exclusion criteria

- Age under 18 and over 35 years
- BMI under 20 and over 27 kg/m^2
- Smoking
- Sleep problems (such as insomnia, daytime hypersomnia or repeated waking up during the night)
- Not in good health
- Medication use that could interfere with the experiment
- Food allergies
- Dietary restrained eaters (F1 > 9)
- Excessive physical activity
- Consumption of more than 10 alcoholic drinks per week
- Change in body weight of more > 5 kg in the last 6 months prior to study entry
- eGFR < 90ml/min/1.73m^2
- Exclusion criteria for MRI (electronic implants, pacemakers, metal fragments in the eyes, skin or body)
- Use of anticoagulants, blood diseases, allergy for lidocain
- Use of gastric acid inhibitors
- All co-morbidities interacting with mobility and muscle metabolism of the lower limbs (e.g. arthrosis, arthritis, spasticity/rigidity, all neurological disorders and paralysis).

#### 4.4 Sample size calculation

To do a sample size calculation a respiration chamber study on the effect of two diets with different macronutrient compositions on energy expenditure was used.

Westerterp *et al.* 1999 report Diet-induced-Thermogenesis of  $14.6 \pm 2.9$  % and  $10.5 \pm 3.8$  % when changing from 29% of energy from protein to 9% of energy from protein in the diet (12). Sample size was calculated using G\*Power version 3.2.1. With the group mean Diet-induced-Thermogenesis change from the past research (12), G\*Power first calculates the effect size. The calculated effect size was 1.212986. With an  $\alpha$  of 0.05 and  $\beta$  of 0.10 (power= $1-\beta=0.90$ ) and an effect size of 1.212986, the program calculates that we need 16 subjects per group.

Taking into account a drop out rate of  $\pm 20\%$ , 20 subjects per condition will be included.

When the subject leaves the respiration chamber before the end of the measurement, this subject is considered as a drop-out.

## 5. TREATMENT OF SUBJECTS

### 5.1 Investigational product/treatment

The 12 weeks dietary intervention period used in this study includes two diets differing in protein content (5En% and 30En%). The 30En% protein group will receive recipes for high-protein meals and in addition protein supplements. The 5En% protein group will receive recipes for low-proteins meals and in addition carbohydrate supplements. The protein and carbohydrate supplements are easily solved in water and can be consumed as shakes.

An example of a high and a low protein menu.

|           | 30En% protein                  | 5En% protein                              |
|-----------|---------------------------------------|--------------------------------------------------|
| Breakfast | cereals
semi-skimmed milk          | Cereals
breakfast drink (juice-based drink)   |
| Shake     | whey-protein (40g)
solved in water | fantomalt (40g)
solved in water               |
| Lunch     | bread
cheese                       | Bread
cucumbersalade                          |
| Snack     | skimmed yoghurt                       | syrup waffle                                     |
| Shake     | whey-protein (40g)
solved in water | fantomalt (40g)
solved in water               |
| Dinner    | nasi goreng
chicken
vegetables  | nasi goreng
peanut butter sauce
Vegetables |

The recommended protein-rich and protein-poor food items will be commercially available in normal Dutch supermarkets.

The chosen protein supplement is an  $\alpha$ -lactalbumine rich whey protein. This protein supplement is chosen because  $\alpha$ -lactalbumine has been shown to increase the ratio of plasma tryptophan to the sum of other amino acids (30). Through its ability to elevate brain serotonin and melatonin levels, tryptophan may have the potential to improve sleep disturbances (as described in the introduction).

### 5.2 Test beverage additional test day

Protein intake is important to stimulate muscle protein synthesis. During the test day, intact casein will be investigated since casein is one of the main proteins that is naturally present in normal milk and it is a representative protein. The same intact casein that has been used previously (MEC 07-3-086, MEC 09-3-078, MEC 10-3-080), will be used again in this study.

All subjects will receive a beverage of a volume of 400 mL water containing intact casein. L-[1-C]phenylalanine labelled milk proteins are produced in collaboration with [name] (Clermont-Ferrand, France) using registered cattle for milk production applying quality process #0000640 in accordance with standard NF V 01-005. Milk proteins were processed to obtain purified casein by the NIZO food research (Nederlands Instituut voor ZuivelOnderzoek, Ede, the Netherlands). During the processing of the milk, total plate count and several tests for micro-organisms were performed (*B. cereus*, *S. aureus*, Coliforms, moulds yeast, Salmonellae and Lysteria) to assure that no contamination occurred during processing. The intact casein was tested according to NIZO's manufacturing specifications conform the performance typical for this grade and product description, before clearance was given for use in human subjects (Appendix D2.1). The casein was stored at -20 °C in the "dietary-kitchen" at the department of Human Biology. The beverage will be uniformly flavoured by adding 5 g of cream vanilla flavour for each litre of beverage (Givaudan, Naarden, the Netherlands (Appendix D2.2)). Drinks will be prepared according to Standard Operating Procedure #RM001, as routinely applied in the kitchen of the department of Human Biology the morning before the start of the test day.

### 5.2.1 Intravenous tracer infusion

The stable isotopic tracers (L-[H5]-phenylalanine, [H2]-tyrosine and L-[1-C]-leucine) will be purchased from Cambridge Isotopes (Andover, USA) and dissolved in 0.9% saline before infusion. Tracer solutions for intravenous administration will be prepared by Basic Pharma following GMP-standards (Appendix D2.3). Continuous intravenous infusion during the entire period of the test day (8½ h, 0.05 µmol/kg/min L-[H5]-phenylalanine, 0.02 µmol/kg/min [H2]-tyrosine, 0.12 µmol/kg/min L-[1-C]-leucine) of the labeled stable isotopes will be performed using a calibrated IVAC 560 pump (San Diego, USA). The phenylalanine, tyrosine and leucine pools will be primed, such that whole body steady state labeling of the amino acids will be achieved within 90 min. Using these tracers in whole body phenylalanine kinetics can be calculated using established tracer models (31), which have been applied in multiple previous studies within our group (24-26, 32-38).

## 6. METHODS

### 6.1 Study parameters/endpoints

#### 6.1.1 *Main study parameter/endpoint*

The main study parameters are energy expenditure, substrate oxidation and sleep.

- energy expenditure (MJ/day), which will be measured via oxygen consumption and carbon dioxide production in the respiration chamber
- substrate oxidation (gram/day); carbohydrate, fat and protein oxidation will be calculated using oxygen consumption, carbon dioxide production and urinary nitrogen excretion, with the formule of Brouwer (39). Urine will be collected during the stay in the respiration chamber. Nitrogen concentration will be measured using a nitrogen analyser.
- sleep (minutes) will be registered continuously with polysomnography

#### 6.1.2 *Secondary study parameters/endpoints*

- body composition (% fat, kg FM and kg FFM), which will be calculated from body volume and total body water using the combined equation of Siri (40). Body volume will be measured with a BodPod. Total body water will be measured with Deuterium dilution according to the Maastricht protocol (41).
- fat distribution (abdominal fat, liver fat and IMCL), which will be determined with MRI and H-MRS
- Regional muscle mass of the upper part of the lower limbs, which will be determined with MRI
- plasma concentrations of glucose (mmol/L), insulin (mU/L) and free fatty acids (FFA, mmol/L) which will be measured before each breakfast in the respiration chamber by drawing one blood sample of 10ml from the antecubital vein of the contra-lateral arm using venapunction
- physical activity (counts/min) one week before baseline measurement and one week before final measurement, which will be measured using a triaxial accelerometer for movement registration (TracmorD; DirectLife, Philips new wellness solutions, Amsterdam, The Netherlands) sensitive to a wide range of body movements.
- mood, feeling of hunger and satiety, which will be measured hourly and before and after each meal, by Visual Analogue Scales (VAS) and by Profile of Mood States (POMS) and State Trait Anxiety Index (STAI) questionnaires (42, 43).
- 6-sulfatoxymelatonin (urinary metabolite of melatonin, ng/day) and 5-hydroxy-3-indole acetic acid (urinary metabolite of serotonin, ng/day) will be measured
- muscle protein synthesis rate, expressed as fractional synthetic rate (FSR):

In order to determine the FSR, the following parameters will be measured in blood and muscle tissue:

- Plasma free phenylalanine and leucine concentration (expressed as  $\mu\text{mol/L}$ )
- Plasma enrichment of L-[ring- $^2\text{H}_5$ ]phenylalanine, L-[1- $^{13}\text{C}$ ]phenylalanine and L-[1- $^{13}\text{C}$ ]-leucine (expressed as mole percent excess (MPE))
- Muscle free and protein bound enrichment of L-[1- $^{13}\text{C}$ ]phenylalanine, L-[1- $^{13}\text{C}$ ]-leucine and L-[ring- $^2\text{H}_5$ ]phenylalanine (expressed as MPE)

- whole body protein turnover: Whole body protein turnover consist of the following rates:

- Exogenous phenylalanine rate of appearance and plasma availability of phenylalanine.
- Total rate of phenylalanine appearance and disappearance (= protein turnover)
- Endogenous phenylalanine rate of appearance (=protein breakdown)

In order to determine these rates, the following parameters will be measured in blood:

- Plasma free phenylalanine, tyrosine and leucine concentration (expressed as  $\mu\text{mol/L}$ )
- Plasma enrichment of L-[ring- $^2\text{H}_5$ ]phenylalanine, L-[ring- $^2\text{H}_2$ ]tyrosine, L-[1- $^{13}\text{C}$ ]phenylalanine, and L-[1- $^{13}\text{C}$ ]-leucine (expressed as mole percent excess (MPE))

## 6.2 Randomisation, blinding and treatment allocation

The study will be conducted in a double-blinded parallel design. The allocation of subjects to the groups with protein intake of 5 or 30 energy percent is randomized. Randomisation will take place by the dietician using a computerized randomization program ('Randomizer' macro in Excel).

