### 3. STUDY DESIGN

[figure not shown]

**Figure 1:** Flow diagram of study design.

The study will have a parallel design and will consist of a short-term (1 week) and long-term (12 weeks) dietary intervention period.

Two days before the baseline measurement, subjects will be fed in energy balance (EB) with protein intake of 15En%. After the baseline measurement, subjects (n=40) will be randomly divided in two groups (2 x n=20). The two applied conditions will differ in the absolute protein content of the meals, including 5En% and 30En% from protein. Fat content will be kept constant in all three conditions regarding the possible effects of fat intake on fat oxidation, resulting in macronutrient compositions of the diets of En% Protein/Carbohydrate/Fat: 5/60/35 and 30/35/35. Both conditions will be compared with the baseline measurement when subjects are fed in energy balance with a macronutrient composition of 15/50/35 En% (Protein/ Carbohydrate/Fat). During the 12 weeks dietary intervention period, subjects will receive recipes prescribed by a qualified dietician. The 30En% protein group will receive recipes for high-protein meals and in addition protein supplements. The 5En% protein group will receive recipes for low-proteins meals and in addition carbohydrate supplements.

To determine energy expenditure and substrate oxidation, subjects will stay in the respiration chamber for 48 hours at baseline, after 1 week and after 12 weeks of an energy balanced diet. During the stay in the chamber, polysomnography will be used to measure wake and sleep phases continuously, in order to determine sleep duration and sleep quality. Every morning blood samples will be taken in fasted state to determine plasma concentrations of glucose, insulin and free fatty acids. Appetite and mood profiles will be measured hourly and before and after each meal, by anchored 100mm visual analogue scales and by POMS and STAI-state questionnaires.

At the start and after 12 weeks, 3-compartment body composition will be determined with the deuterium dilution technique combined with densitometry (BodPod). To investigate fat distribution MRI and  $^1\text{H}$ -MRS will be used. Abdominal fat will be assessed at baseline, and liver fat and intramyocellular lipid (IMCL) content, as well as the mass of the vastus lateralis muscle will be measured at baseline and after 12 weeks.

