## **10. ADMINISTRATIVE ASPECTS AND PUBLICATION**

### **10.1 Handling and storage of data and documents**

Subjects' personal information will be confidentially handled during the study, according to the Dutch Personal Data Protection Act (Wet bescherming persoonsgegevens; Wbp). Results will be linked to the intervention and not to individual subjects. Subject numbers (e.g. number 1) in combination with treatment codes (5En% protein, code A; 30En% protein, code B) will be used throughout the study. Only the researchers are familiar with subject information, so privacy of personal information is guaranteed. If desirable, subjects will be informed about their personal study results at the end of the study. Collected body material (urine and blood) will be destroyed after publication of the results. Personal data will be kept for a period of 15 year, which is the legal time to keep medical data. Hereafter the data will be destroyed.

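### The protocol promises matched groups and a double blind, but no described step produces the match and the diets cannot be double-blinded

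*Protocol*

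**What the plan says.** **Groups.** Section 4.1 describes "normal weight subjects (20 subjects within each condition) matched in BMI, age and gender". Section 3 says that, after the baseline measurement, "subjects (n=40) will be randomly divided in two groups (2 x n=20". Section 6.2 names the tool and the person: "Randomisation will take place by the dietician using a computerized randomization program ('Randomizer' macro in Excel". It adds nothing on strata, blocks, pairs, minimisation or concealment.

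**Blinding.** Section 6.2 states: "The study will be conducted in a double-blinded parallel design". It does not say who is blinded or how. The Summary and section 3 describe a randomised parallel design and do not mention blinding.

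**What subjects receive.** Section 5.1: "The 30En% protein group will receive recipes for high-protein meals and in addition protein supplements". Section 3, for the other arm: "The 5En% protein group will receive recipes for low-proteins meals and in addition carbohydrate supplements". The example menus in 5.1 differ visibly, and the shakes are whey protein in one arm and a carbohydrate product in the other.

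**Codes.** Section 10.1 says that, together with subject numbers, "treatment codes (5En% protein, code A; 30En% protein, code B) will be used throughout the study".

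**Analysis.** Section 8.2 compares the conditions by one-way ANOVA without covariates. Section 8.3 adds multiple regressions on gender, age and BMI for the same outcomes.

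**The concern.** Two properties are claimed that a reader of the eventual report would rely on.

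The first is balance. Energy expenditure, a main endpoint, is measured in MJ/day, where gender and body size would be expected to matter. If nothing in the allocation enforces the match, section 4.1 is not a description of the trial. If someone arranges the match by hand, allocation is no longer purely random.

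The second is blinding. Sleep is a main endpoint and its stages are scored from polysomnography (PSG). Abdominal fat and regional muscle mass come from segmented or measured MRI images. Appetite, subjective sleep, mood and anxiety come from VAS, POMS and STAI, completed by the subjects. The label suggests that all of these are protected from knowledge of the arm. For the self-reports this cannot be true; for the image and sleep reads it is not shown.

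**Working it through.** **1. The plan's own size.** Section 4.4 gives diet-induced thermogenesis (DIT) of 14.6 (SD 2.9)% and 10.5 (SD 3.8)%.
- Pooled SD = √((2.9² + 3.8²)/2) = 3.380; effect size = 4.1/3.380 = 1.213, as stated.
- Two-sided t-test at 0.05: power 0.894 with 15 per group and 0.913 with 16. So 16 per group, and 16/0.80 = 20 per condition. The figure reproduces.

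**2. Matching against allocation.** Section 4.1 promises balance on three factors. Sections 3 and 6.2 describe random division into 2 × 20 by a macro. None of these steps controls BMI, age or gender.

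**3. Blinding against intervention.**
- *Subjects* follow recipes that are high or low in protein for 12 weeks and mix different supplements. They can recognise their diet.
- *The dietician* runs the randomisation (6.2). A qualified dietician also prescribes the recipes (3) and prepares the arm-specific chamber meals (6.3.2, energy intake). No separation of these roles is described.
- *Researchers* use codes whose key is printed in the protocol.
- *Assessors*: no section states that PSG scoring or MRI reading is masked, and none states that it is not.

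**4. Illustration of chance gender imbalance.** The gender split is not given; assume 20 men and 20 women and an unstratified 20/20 division. The number of men k in one arm is hypergeometric: P(k) = C(20,k)·C(20,20−k)/C(40,20).
- P(10 v 10) = 184,756²/137,846,528,820 = 0.248
- P(11 v 9, either way) = 2 × 167,960²/137,846,528,820 = 0.409
- P(12 v 8, either way) = 2 × 125,970²/137,846,528,820 = 0.230
- P(difference of at least 4 men) = 1 − 0.248 − 0.409 = 0.343
- P(at least 6) = 0.343 − 0.230 = 0.113

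With 16 or 12 men among the 40, the chance of a difference of at least 4 is 0.33 or 0.30.

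**5. What that could mean in MJ/day.** The protocol gives neither a level of 24-h expenditure nor a male-female gap. Assume 8 to 11 MJ/day and a gap of 1 to 3 MJ/day.
- 4.1 DIT points correspond to 0.041 × 8 = 0.33 up to 0.041 × 11 = 0.45 MJ/day.
- A 12 v 8 split shifts the unadjusted arm difference by (12 − 8)/20 = 0.20 times the gap, or 0.20 to 0.60 MJ/day.
- Ratio to the planning effect: 0.20/0.451 = 0.44 up to 0.60/0.328 = 1.83.
- The chance of an imbalance worth at least the planning effect runs from 0.004 to 0.34 over these assumptions.
- Over all allocations the difference in the proportion of men averages zero, with SD 0.160. Gender alone therefore adds a random component with SD 0.16 to 0.48 MJ/day to the unadjusted difference.

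**The case against.** The strongest reply is that section 6.2 names a tool and not its settings. The macro might randomise within strata or matched pairs, which would reconcile sections 4.1 and 6.2. A reader might infer that the allocation is unstratified, but that rests on silence. What stands is that a match is promised and no described step delivers it. Allocation precedes analysis, and 6.2 is where this protocol sets it out.

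A reader might also infer that gender imbalance will be as large as the expected effect. The documents do not support this. It depends on assumed MJ/day figures and, under the assumptions above, is a chance event of at most about one in three. On the DIT percentage scale used for planning, a 12 v 8 split would need a gender gap of 4.1/0.20 = 20.5 points, more than either mean. Nor is it bias: under random allocation the expected imbalance is zero. Comparison with each subject's baseline (sections 3 and 8.2) would remove a constant gender offset if change is analysed, and the 8.3 regression could help. However, 8.2 does not specify a change score and 8.3 does not say that it adjusts the diet effect.

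Unequal arms from a coin toss per subject should not be inferred either: section 3 fixes 2 × 20.

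Finally, a reader might infer that the assessors know the arm. The documents do not say so; a printed key makes unblinding possible without proving it. Chamber gas samples are selected and processed by computer, which leaves little room for judgement in energy expenditure. It is also not stated that the dietician who randomises is the one who cooks. None of this restores a double blind for subjects who recognise their diet and a dietician who runs the allocation.

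**Conclusion.** The point holds in two parts, both internal to the protocol. The match in section 4.1 has no mechanism in sections 3 or 6.2. The double blind in section 6.2 is incompatible with the intervention in sections 3 and 5.1 and is weakened further by the printed key in section 10.1. Shielding of sleep scorers and MRI readers is not shown, and VAS, POMS and STAI must be read as unblinded.

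The blinding part needs no numerical assumption. The figures for balance (34% and 11%) are illustrative: they assume 20 men, 20 women and no stratification. Their consequence is lost precision in the covariate-free MJ/day comparison, of a size set by an assumed male-female gap. The change should be made because it is nearly free and corrects what the trial can claim.

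**What to change.** - **4.1 and 6.2, allocation.** Replace the word 'matched' with permuted-block randomisation stratified by gender. An existing team member who does not deliver the diet prepares and holds the list. Assignment after the baseline measurement, already in section 3, stays. With blocks of 2 and 4 in random order, for example, the arms can differ by at most 2 men; the total may miss exactly 20/20 slightly if a block is left incomplete.
- **8.2, analysis.** Include gender and the baseline value in the diet comparison.
- **6.2, blinding.** Replace 'double-blinded' with: subjects and dietician unblinded; PSG scoring, MRI/MRS segmentation and laboratory analysis blinded.
- **10.1, codes.** Use neutral subject codes and keep the A/B key from those assessors. Keep urinary nitrogen results from the PSG and MRI readers too, because a diet contrast of 5 v 30 En% protein would tend to reveal the arm.
- **Reporting.** Describe VAS, POMS and STAI as unblinded.

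Cost: one list, neutral file coding and edits to four sections. No extra subjects or staff.
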